### Safety Assessment

An independent data and safety monitoring committee evaluates the progress of the trial and assesses the safety data that may be requested during the trial. An adverse event (AE) is defined as any undesirable experience that participants undergo during the trial period, whether it is associated with the intervention or not. Participants will be instructed to report any AEs to the research team at any time. All details of AEs such as time of occurrence, severity, management, and causality to the intervention will be recorded on case report forms (CRFs). There are nine common AEs related to ACE: (1) lingering discomfort; (2) local hematoma or subcutaneous bleeding; (3) local swelling; (4) local induration; (5) severe pain; (6) thread extrusion; (7) local itching; (8) elevated body temperature after embedding the thread; and (9) local redness, swelling, heat, and pain after embedding the thread [27]. All AEs will be followed up from the date they are brought to the investigator’s attention until the AE is resolved. In the event of an emergency medical situation, the individual’s randomization code and group allocation will be identified via a standard operational procedure.

### Quality Control

Before recruitment, the entire research team including acupuncturists, operational assistants, and research nurses were required to attend a training workshop. This was done before the trial to ensure their strict adherence to the study protocol and familiarity with the trial administration process. They were also provided with a written protocol and standard operation procedure documents. The 2 acupuncturists who will administer the treatment each have acupuncture licenses from the Chinese Ministry of Health and have over 5 years of experience in ACE application. The data collected in this trial comprise information recorded in CRFs and information on the RCAT, TNSS, TOSS, and blood routine examinations. Data will be entered using the double-entry method. The data quality will be checked regularly by research assistants and overseen by monitors. Data monitoring will be conducted regularly following standard operation procedures set by the Guangdong International Clinical Research Center of Chinese Medicine (Guangzhou, China). Audits will be performed regularly by the Department of Science Research at the Guangzhou University of Chinese Medicine. All modifications will be marked on the CRFs. Data managers will then recheck the data before logging them and promptly notify the research team if any discrepancy is found. The database will be locked after all data have been cleaned. If participants withdraw from the trial either during the treatment period or the follow-up phase, they are not required to provide any reasons. The withdrawal rate will be analyzed via statistics.

### Sample Size Calculation

Our preliminary study [28] indicated that the 3-month recurrence rate of the ACE group should be at least 5% lower than that of the Sham ACE group to be clinically significant. Using α=0.025 (unilateral), β=0.2, △=5%, and K=1, the sample size was estimated based on the comparison of two sample rates in the optimization test. The sample size in each group was calculated to be 52. Since the effectiveness of any treatment was not 100%, patients with ineffective treatment in this study could not be included in the assessment of recurrence, so the loss of follow-up rate in this study was 20%, which amounted to 126 cases. The \following equation is used to calculate the sample size, which refers to the estimated number of patients to be enrolled in the study:

[figure not shown]

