### Randomization and Allocation Concealment

A block randomization sequence was generated by SAS software (version 9.2; SAS Institute Inc), which was performed by Guangdong Provincial Hospital of Chinese Medicine’s Key Unit of Methodology in Clinical Research. Eligible participants will be randomly assigned to either the ACE group or the sham ACE group at a ratio of 1:1. An independent researcher will prepare treatment cards, on which a serial number and one of 2 names are printed, each representing one of the 2 groups. This independent researcher will be responsible for selecting and adding intestinal thread to the injection needles according to the respective groups. Treatment allocations will be stored in password-protected files and held independently by staff of the Key Unit of Methodology in Clinical Research. While receiving the first treatment, the participants will be given sequential treatment cards from independent researchers to ensure adequate concealment. The participants will be allocated into one of 2 groups according to the name printed on their treatment card.

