### Statistical Analyses

Intentional therapeutic analysis will be adopted, with missing values estimated using the last observation carried forward method. Mean and SD (for continuous variables that obey normal distribution), median and quartile (for continuous variables that do not obey normal distribution), and frequency and percentage (for classified variables) will be used for the statistical description. According to the numerical characteristics of the variables, quantitative data such as age, height, and weight of the 2 groups will be compared using a *t* test or the Wilcoxon rank sum test. The chi-square test or Fisher exact probability method will be used to compare qualitative variables, such as sex and nationality between the 2 groups. Cox regression analysis will be carried out with recurrence outcome and time of first recurrence as dependent variables, and the differences in survival curves between both groups will be compared. SPSS software (version 23.0; IBM Corp) will be used for statistical analysis. A 2-sided test will be used for all statistical inferences, and *P*<.05 will be considered statistically significant.

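### The 52 per group cannot be squared with both the 5% difference in the sample size section and the planned test: it is far too few to detect 5 points, or 5 points is a margin that the stated analysis never tests

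*Protocol article*

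**What the plan says.** The article's Sample Size Calculation section cites a preliminary study for a threshold at 3 months: "recurrence rate of the ACE group should be at least 5% lower than that of the Sham ACE group to be clinically significant". It then lists the inputs, "Using α=0.025 (unilateral), β=0.2, △=5%, and K=1", and says that "the sample size was estimated based on the comparison of two sample rates in the optimization test". The result is "The sample size in each group was calculated to be 52", raised for 20% loss to a total of 126. The text states no expected recurrence rate for either arm. The equation follows as a figure that is not available here.

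The Statistical Analyses section says that "Cox regression analysis will be carried out with recurrence outcome and time of first recurrence as dependent variables" and that the survival curves of the two groups will be compared. All inference is two-sided at P<.05. It mentions no 5-point margin.

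**The concern.** Δ=5% is the only effect size printed, and it stands beside α, β and the allocation ratio as an input. The most direct reading is therefore that the trial has 80% power for a 5-point reduction in recurrence. A group size of 52 is very small for a 5-point difference between two proportions.

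The other possible reading is that 5 points is a margin to be exceeded. That changes the arithmetic, but it also changes the hypothesis, and the analysis section does not follow.

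Recurrence at 3 months is the primary outcome. On the first reading, a non-significant result could be taken as evidence against a clinically relevant effect that 52 per group would usually miss. On the second, a significant Cox result could be taken as showing a reduction beyond 5 points when only a reduction beyond zero was tested.

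**Working it through.** **Inputs from the article.** One-sided α=0.025 (z=1.960); β=0.2 (z=0.842); Δ=0.05; ratio 1:1; 52 per group. The two-sided P<.05 of the analysis section corresponds to one-sided 0.025 in the favourable direction, so sidedness is not the problem. All recurrence rates below are assumptions, because the text gives none. Write p1 for sham, p2 for ACE, and (1.960+0.842)² = 7.849.

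**The stated figure.** 52 × 1.2 = 62.4, so 63 per group and 126 in total. This confirms that 52 is the evaluable number on which enrolment is built. The 52 itself cannot be reproduced from the printed inputs alone, so both possible roles of Δ were tried.

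**(a) Δ is the difference to detect.** n = 7.849 × [p1(1−p1) + p2(1−p2)] / 0.05². For 5% vs 0%: 7.849 × 0.0475 / 0.0025 = 149.1, so 150. Power uses the same variance with n=52.

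| Sham vs ACE (assumed) | n per group for 80% power | Power with 52 per group |
|---|---|---|
| 5% vs 0% | 150 | 38% |
| 10% vs 5% | 432 | 16% |
| 20% vs 15% | 903 | 10% |
| 30% vs 25% | 1,248 | 8% |
| 50% vs 45% | 1,562 | 7% |
| 80% vs 75% | 1,091 | 9% |

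Other formulas do not rescue 52. At the extreme pair of 5% vs 0%, pooled variance gives 152, one-sided α=0.05 gives 120 and the arcsine form gives 78; a continuity correction raises n. Reading 5% as a relative reduction gives 6,275 at a sham rate of 50% and 152 even at a sham rate of 100%.

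Without a margin, the difference that 52 per group detects with 80% power solves 7.849 × [p1(1−p1) + p2(1−p2)] / (p1−p2)² = 52:
- sham 30%: ACE 9%, 21 points
- sham 50%: ACE 24%, 26 points
- sham 70%: ACE 44%, 26 points

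The pooled form gives up to 27 points.

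**(b) Δ is a superiority margin.** n = 7.849 × [p1(1−p1) + p2(1−p2)] / (p1−p2−0.05)². For 50% vs 20%: 7.849 × (0.25+0.16) / 0.25² = 51.5, so 52. For 80% vs 50% the result is the same. For 30% vs 5% it is 50.5, so 51.

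The true difference that 52 requires depends on the sham rate:
- The low end is about 21 points: 21% vs 0% gives 7.849 × 0.1659 / 0.16² = 50.9, so 51.
- The high end is about 31 points, at a sham rate of 65% (ACE 34%).
- A sham rate of 20% is too low: even with no ACE recurrence it needs 56.

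**The test under (b).** The hypothesis would be that the reduction exceeds 5 points. A Cox test at P<.05 asks whether the hazard ratio differs from 1. A hypothetical result shows the gap on the rate scale. Take 26/52 (50.0%) against 15/52 (28.8%), a difference of 21.2 points. The standard error is √(0.2500/52 + 0.2053/52) = 0.0936, so the 95% interval is 21.2 ± 18.3, or 2.8 to 39.5 points. It excludes zero but not 5 points.

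**The case against.** The strongest reply is that 5% was never the expected effect. The phrase about being at least 5% lower reads as a threshold, the α is one-sided, and optimization test may be a translation of superiority test. All three fit a margin formula, under which 52 follows from unremarkable rates. No sentence claims in so many words 80% power for a true 5-point difference. The equation that would settle the matter is a figure that cannot be seen here, and its absence is no fault of the plan. A decision rule may also sit in an analysis plan that is not shown.

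Much of this stands. A reader might infer that 52 cannot follow from Δ=5% on any basis. The documents do not support that, because the margin formula gives 52 at 50% vs 20%. On that reading, the low power figures in (a) are beside the point. A reader might also infer that the Cox analysis is wrong in itself. It is not: it is a valid test of no difference, and it falls short only if 5 points is a margin.

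The objection does not remove the inconsistency. The margin reading rescues the arithmetic by giving Δ a role that the stated analysis ignores, and it relies on a true difference of at least four times the only one printed in the text. The difference reading matches the stated test but makes 52 impossible. The finding rests on what the two sections state, not on the missing figure.

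**Conclusion.** Wrong as written. Neither reading makes the sample size and analysis sections agree.

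- If 5 points is the difference to detect, 52 per group falls short by a factor of about 3 at the most favourable rates (150/52) and about 17 to 30 at sham rates of 20% to 50% (903/52 to 1,562/52). This needs no guess at the missing rates, because it fails for every pair.
- If 5 points is a margin, 52 is sound only with an unprinted true difference of about 21 to 31 points, and the stated primary analysis does not test the margin.

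Which reading the sponsor intended cannot be decided from the article. The conclusion assumes the normal-approximation formulas for two proportions, as the text's reference to comparing two rates implies.

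**What to change.** State in the sample size section the two assumed 3-month recurrence rates, their source, and whether Δ is the difference to detect or a superiority margin. Then do one of the following:

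- **Difference to detect:** drop 80% power for 5 points and state what 52 evaluable per group can detect without a margin, about 21 to 26 points for sham rates of 30% to 70%.
- **Superiority margin:** state the expected difference, and claim that the margin is met only if the 95% confidence interval for the reduction in 3-month recurrence lies wholly beyond 5 points. The Cox analysis can stay as the comparison of time to recurrence.

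This changes wording in the protocol and analysis plan and adds no enrolment. The price is a less favourable stated detectable effect in the first case and a stricter success criterion in the second. Recruitment is under way, so the change should be made and dated before outcome data by group are seen.

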### Outcome Measurement

For an evaluation of the primary and secondary outcome measures, the participants are required to complete 2 questionnaires, the Total Ocular Symptom Score (TOSS) and the Total Nasal Symptom Score (TNSS) [19]. These questionnaires will be completed at the beginning of each of the 4 treatment sessions (from week 2 to week 5) and in weeks 8, 12, and 16 during each follow-up session. During the follow-up process, the participants need to independently record their Rhinitis Control Assessment Test (RCAT) scores weekly [20]. In addition, the participants will be asked to complete diaries throughout the trial. The primary outcome is the recurrence rate 3 months after discontinuation. Once the treatment-effective participants discontinue the medication (RCAT score less than 21 points), they will immediately enter the follow-up period. If a relapse occurs, the relapse time will be promptly recorded, and the follow-up will conclude. Otherwise, the participants will continue to be monitored until 3 months after discontinuation of medication. RCAT is one of the most commonly used rhinitis control scales, and its reliability, validity, and responsiveness have been widely verified [21,22]. A score of 21 corresponds to the validated RCAT score of 25, which determines the controlled state of rhinitis. When RACT ≤21, it indicates an uncontrolled state of AR and the starting point for treatment [23]. RCAT is a simple self-rating scale that allows patients to assess their AR control at home and helps assess the success of long-term repeated treatment interventions [20,24]. TNSS evaluates 4 nasal symptoms: nasal obstruction, sneezing, rhinorrhea, and nasal itch. The symptoms are self-assessed and recorded by participants using a 5-point scale (0=no symptoms; 1=mild symptoms; 2=moderate symptoms; 3=severe symptoms; 4=very severe symptoms) [23]. TNSS scores range from 0 to 16, with low scores indicating lighter nasal symptoms. TOSS assesses eye symptoms, including redness, itchiness, and tearing. Each symptom is assessed on a scale between 0 and 3 (absent to most severe), with a total score from 0 to 9 [19,25]. The score represents an average for both eyes. The secondary outcomes include (1) changes in TNSS and TOSS score from baseline to weeks 8, 12, and 16; (2) response to interventions, defined as participants with a change in TNSS score of ≥0.5 from baseline; (3) and serum levels of tumor necrosis factor-alpha (TNF-α), IFN-γ, IL-4, IL-17, and IgE, measured by enzyme-linked immunosorbent assay according to the manufacturer's protocol (Bio-Techne).

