The purpose of this trial is to reduce the recurrence of rhinitis, relieve symptoms, and achieve clinical benefit by using ACE as a nondrug therapy. Previous articles about ACE for the treatment of AR lack placebo-controlled, high-quality research [26]. Therefore, it is necessary to provide high-quality research in this domain. We designed this RCT to examine whether ACE treatment decreases recurrence and improves symptoms such as sneezing, clear watery nasal discharge, itchy nose, and nasal congestion in patients with AR. The main limitation of this study is its single-blind design. Another potential limitation is the possibility of patient attrition due to the requirement of undergoing treatment over 4 weeks, totaling 4 times. Another limitation is our inability to design double-blind trials due to the material and design of the embedding needles. Moving forward, our aim is to develop improved embedding needles that align more closely with the requirements of double-blind testing, thereby enhancing the international promotion of this therapy. The strengths of this study include the use of a randomized controlled design, with all patients being followed up. Both subjective and objective data will be collected in this study to examine the effectiveness of ACE in treating AR. Another advantage is that it focuses on decreasing recurrence. The results of this study could improve the treatment outcomes of patients with AR. We posit that this research will provide important insights into the efficacy of ACE treatment for AR and generate robust data for the foundation of future research in this field.

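### The 20% allowance was multiplied on rather than divided out, so 126 enrolled leaves about 50 evaluable per group instead of 52, and it is unclear which losses the 20% covers

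*Protocol article*

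**What the plan says.** All the figures are in the Sample Size Calculation section of the protocol article. The inputs are given as "Using α=0.025 (unilateral), β=0.2, △=5%, and K=1", and the result as "The sample size in each group was calculated to be 52". The section then explains that "patients with ineffective treatment in this study could not be included in the assessment of recurrence", and continues directly: "so the loss of follow-up rate in this study was 20%, which amounted to 126 cases". No other allowance is stated.

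Other sections bear on what the 20% has to cover:

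- Randomization and Allocation Concealment fixes equal allocation: "Eligible participants will be randomly assigned to either the ACE group or the sham ACE group at a ratio of 1:1".
- Outcome Measurement limits the recurrence follow-up to responders: "Once the treatment-effective participants discontinue the medication (RCAT score less than 21 points), they will immediately enter the follow-up period".
- Quality Control provides for withdrawal during treatment or follow-up, without a reason being required.
- The Discussion adds: "Another potential limitation is the possibility of patient attrition due to the requirement of undergoing treatment over 4 weeks, totaling 4 times". No rate is attached.
- Statistical Analyses announces what reads as an intention-to-treat analysis, with last observation carried forward for missing values and a Cox model for time to first recurrence.

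**The concern.** There are two separate problems in the step from 52 per group to 126 in total.

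The first is arithmetic. An allowance for losing a fraction d of those enrolled is made by dividing the required number by (1 − d). Multiplying by (1 + d) always falls short, because the loss applies to the larger, enrolled number. If that was done here, the three stated figures (52, 20% and 126) cannot all be true together.

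The second is the meaning of the 20%. Non-response occurs before the period at risk of recurrence begins. Dropout can occur during treatment or over the 3 months afterwards. The section uses the name of the second kind of loss and the explanation of the first. If one figure has to absorb both, that should be said. If it stands for non-response alone, the expected evaluable number is lower than the section implies.

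At stake is whether the enrolment target delivers the evaluable number that the article itself says the primary outcome needs.

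**Working it through.** **Inputs.** From Sample Size Calculation: 52 evaluable per group (104 in total), 20% loss, 126 enrolled, one-sided α = 0.025, β = 0.2. From Randomization and Allocation Concealment: 1:1 allocation. No dropout rate is given anywhere, so the rates in step 5 are assumptions.

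**1. Reproducing 126.** Multiplying per group: 52 × 1.2 = 62.4, rounded up to 63; 2 × 63 = 126. This matches exactly. Multiplying the total instead gives 104 × 1.2 = 124.8, rounded up to 125, so the stated figure fits multiplication with rounding within each group.

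**2. The inflation that keeps 52.** n / (1 − d) = 52 / 0.80 = 65 per group; 2 × 65 = 130. The stated target is 4 short.

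**3. What 126 delivers.** 126 × 0.80 = 100.8 evaluable, or 50.4 per group. The largest loss that 126 can absorb while leaving 104 is 1 − 104/126 = 0.175, or 17.5%.

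**4. Effect on power.** Suppose 52 per group gives 80% power at the effect it was sized for. Then, for n evaluable per group,

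power = Φ[(1.960 + 0.842) × √(n/52) − 1.960].

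At n = 50.4: √(50.4/52) = 0.9845; 2.802 × 0.9845 − 1.960 = 0.799; power ≈ 78.8%.

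**5. If the 20% is non-response only.** Apply an assumed further dropout w to the 50.4 who remain, and find the enrolment that would restore 52:

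| Assumed w | Evaluable per group, 50.4 × (1 − w) | Enrolment, 2 × ⌈52 / (0.80 × (1 − w))⌉ |
|---|---|---|
| 5% | 47.9 | 138 |
| 10% | 45.4 | 146 |
| 15% | 42.8 | 154 |
| 20% | 40.3 | 164 |

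The formula in step 4 gives about 76.7% power at 47.88 per group (2.802 × 0.9596 − 1.960 = 0.729) and about 69.4% at 40.32 per group (2.802 × 0.8806 − 1.960 = 0.507). This step holds only on that one reading of the 20%.

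**The case against.** The strongest reply is that the slip is immaterial. It is 4 patients in 130 and 1.2 points of nominal power. The 20% is a planning guess without a stated source, and the gap between 17.5% and 20% lies well within its uncertainty. That stands as an argument about size. It does not make the figures consistent: no 20% loss from 126 leaves 104.

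A second reply concerns what the 20% covers. A reader might infer that it is for non-response only and that dropout has no allowance at all. The documents do not support that as a fact. The section calls the figure a loss to follow-up rate and does not exclude other losses, so a single allowance for every non-evaluable patient is also a fair reading. Naming attrition as a limitation in the Discussion does not show that no allowance was made for it. What stands is that the label and the reason do not match.

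A third reply is that the analysis may keep everyone. With last observation carried forward, non-responders and dropouts could stay nominally in an intention-to-treat analysis, and a Cox model would censor patients lost during follow-up rather than delete them. This is fair, and it is why the evaluable count depends on the population analysed. But neither device restores unobserved recurrence, and the sample size section itself says that non-responders cannot be assessed.

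**Conclusion.** The point holds, and it is minor. The enrolment figure comes from multiplying by 1.2 where dividing by 0.80 was needed. Under the article's own 20% loss, 126 yields about 50 evaluable per group instead of 52, with nominal power of about 79% instead of 80%.

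The power figure is conditional on 52 being right. The article states no recurrence rates, and the equation does not appear in the copy read, so the effect behind 52 cannot be checked. A reader might infer that enrolling 130 would make the trial adequately sized. It would only make the inflation step consistent with 52.

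The scope of the 20% is unclear rather than shown to be wrong. A reader might also infer a substantial loss of power from dropout. That needs both the non-response-only reading and a dropout rate that the documents do not give, so the 48 to 40 evaluable per group (for an assumed 5% to 20% dropout) show sensitivity and are not a finding about this trial.

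**What to change.** In Sample Size Calculation, do one of the following:

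- keep 126 and state that, with a 20% loss, it yields about 50 evaluable per group and about 79% nominal power at the effect for which 52 was calculated; or
- correct the inflation to 52/0.80 = 65 per group and the target to 130.

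In either case, say whether the 20% stands for non-response, dropout or both. If both, give the two components. Make the statement agree with the population analysed for recurrence, which Outcome Measurement confines to responders while Statistical Analyses points to all randomised patients. If all randomised patients are to be analysed, only true dropout needs an allowance.

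The cost is a few restated sentences or, if the sponsor prefers the second option, four more patients. The article reports that recruitment is under way, so the wording should be settled before enrolment closes.
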